## Statistical analysis

### Analysis principles and general considerations

Primary and where appropriate, secondary outcome testing will be conducted on an ‘intention-to-analyse’ basis irrespective of whether scan processing was successful or not◦ Processing will be considered successful when an ASPECTS (0-10) or CTA result (occlusion/no-occlusion or scalar collateral score) is provided, or when arterial hyperattenuation or haemorrhage is detected.◦ We will record all software failures whether these occur at the scan upload, scan processing, or results output stage.We will use mean (standard deviation, SD) or median (inter-quartile range, IQR) to represent the distribution of parametric and non-parametric data, respectively. We will use n (%) for categorical data.Where possible, we will use diagnostic accuracy statistics as the principal method in RITeS for comparing software and expert human results. With expert human results as the reference standard, we will calculate true/false positive/negative cases (TP, FP, TN, FN, respectively) and derive sensitivity (TP/TP+FN), specificity (TN/TN+FP), positive predictive (TP/TP+FP), negative predictive (TN/TN+FN), and accuracy (TP+TN/TP+TN+FP+FN) percentages as standard. We will calculate 95% confidence intervals for each using the Wilson score method^37^. ◦ For all diagnostic accuracy testing we will include random-effects meta-analysis modelling of individual patient data (i.e. a one-step meta-analysis) to provide overall estimates of sensitivity and specificity, to assess variation within and between the 10 RITeS studies, and to account for clustering of individual study results^38^,^39^.◦ For each of the 10 RITeS studies, we will use the PROBAST method for assessing risk of bias in diagnostic modelling^40^. For all comparisons of software and expert human results, we will review side of affected brain data to ensure ASPECTS and CTA results are correctly matched for each cerebral hemisphere, i.e. matched results require same score and side. We will separately test whether knowledge of affected side impacts the accuracy of e-ASPECTS results, see secondary outcomes below.Bland-Altman plots^41^ will be used to visually compare software and expert human results, comparing mean score differences to assess the magnitude, direction and distribution of error and will use ± 1.96 SD to determine the range of agreement^42^. For software and expert human results to be considered equivalent, we will set maximum clinically acceptable limits of agreement for individual scores, specified in the relevant sections below.Krippendorff’s Alpha^43^ (K-alpha) will be used to assess reader (human-human and human-software, as necessary) agreement. K-alpha is generally more robust than kappa in this context since it can handle categorical and ordinal data, works where there is missing data, adjusts for small sample sizes, and includes multiple observers simultaneously^43^,^44^. K-alpha results are interpreted similarly to kappa with scores ranging from -1 (perfect disagreement) to +1 (perfect agreement). We will therefore also use the Landis and Koch method for interpreting K-alpha results (as commonly used for kappa): 0.00–0.20=slight agreement, 0.21–0.40=fair agreement, 0.41–0.60=moderate agreement, 0.61–0.80=substantial agreement and 0.81–1.00=almost perfect agreement^45^.Other specific statistical tests are listed in the following sections.For multivariable testing, we will check for multicollinearity between included variables by identifying variance inflation factors (VIF) >5. Where multicollinearity is detected, we will run separate (but otherwise equivalent) multivariable regression models for each of the internally correlated variables.We will not impute but will report missing data (proportions of data missing for each variable and observations not included in analyses).We will use SPSS, IBM Corporation (Armonk, USA) and/or R (https://www.r-project.org/) statistical software for all analyses. We will preferentially report 95% confidence intervals, but where appropriate, we will report p-values.

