### Secondary outcomes

**
*1. e-ASPECTS processing success and factors influencing accuracy.*
** To present the most complete picture available, we will use the entire RITeS sample for these analyses (i.e. not just the representative sample) but we will also include a sensitivity analysis of the representative sample.

We will report the proportion of scans successfully and unsuccessfully processed by e-ASPECTS and collate reasons cited by e-ASPECTS for any processing failures. We will use summary statistics to describe and compare the subgroups of scans that were successfully versus unsuccessfully processed. This will include patient and radiological factors (see Table 4).

To determine the influence of patient and radiological factors on the accuracy of ASPECTS results produced by e-ASPECTS software, we will perform multivariable ordinal logistic regression using the variables pre-specified in Table 5. The dependent variable will be the absolute difference in ASPECTS between e-ASPECTS and expert human readers (i.e. scalar, 0-10).

For any variables found to be significantly associated with poorer e-ASPECTS results on regression testing (i.e. independently associated with greater difference between e-ASPECTS and expert human reader scores), we will also calculate and compare diagnostic accuracy figures (as above) for each of the subgroup arms (for these analyses only, continuous data will be dichotomised as per Table 5).

Finally, to account for (the as yet unknown) covariates that alter e-ASPECTS diagnostic accuracy figures, we will derive covariate-adjusted ROC curves (AROC)^50^.

**
*2. Identification of CTA obstruction and collateral scoring by e-CTA versus expert human readers.*
** There are two components to the e-CTA output: 1. Where ICA-MCA occlusion is identified, the location is categorised either proximal (ICA/proximal MCA) or distal (distal MCA). Other arteries are not assessed.2. MCA collateral scoring (modified Tan *et. al*. 2009)^51^ is given for all cases on the scale 0 = no collaterals (<10% of affected MCA territory compared to contralateral side), 1 = poor (10–50%), 2 = good (50–90%), 3 = excellent (>90%) collaterals (i.e. includes normal scans).

The expert human rated CTAs available to RITeS include similar scoring methods for comparison with e-CTA outputs, but also additional measures such as degree of arterial patency (i.e. from fully patent through increasingly obstructed to occluded)^22^.

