### 2c. Association between e-ASPECTS or e-CTA results and clinical outcome after stroke

We will use the entire RITeS samples of NECT and CTA for these analyses but also perform sensitivity analyses using the representative NECT sample.

In separate multivariable analyses, we will test whether the three main software outputs of e-ASPECTS (ASPECTS result) and e-CTA (ICA-MCA axis occlusion, MCA territory collateral score) are independently associated with stroke outcome. We will include the following variables in each model since these are already known to be associated with outcome after stroke: age, NIHSS, time from stroke onset, treatment with alteplase and/or thrombectomy (vs no treatment). The dependent variable in each model will be functional outcome after stroke. Assessment of functional outcome after stroke varies among the RITeS trials and includes either the modified Rankin Score (mRS) at 90 days, or the Oxford Handicap Scale (OHS) at 6 months from stroke onset. Both mRS and OHS are 7-point scalar ranging from normal (0) through increasing disability (1–5), to death (6). We will use multivariable ordinal logistic regression to calculate common odds ratios for good outcome, presented as per Table 10.

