**Table 3. T3:** Planned assessment of radiological characteristics of the entire RITeS dataset.

Radiological Finding		N (%) or Median (IQR)
Ischaemic brain changes	None	
	Subtle (e.g. loss of grey-white margins)	
	Obvious (e.g. hypoattenuation relative to normal white matter +/- swelling)	
Ischaemic location	MCA territory	
	Other cerebral	
	Brainstem or cerebellum	
	Cortical	
	Subcortical	
Hyperattenuating arteries	List location	
Haemorrhage location	Deep	
	Lobar	
	Intraventricular	
	Extra-axial	
Structural stroke mimic	List type (e.g. tumour, inflammation, collection)	
Pre-stroke brain changes	Atrophy	
	Leukoaraiosis	
	Old Stroke lesions	
CT slice thickness	Thin (≤ 1 mm)	
	Medium (> 1 mm ≤ 5 mm)	
	Thick (> 5 mm)	

**Table 4. T4:** Planned univariable comparison of scans successfully versus unsuccessfully processed by e-ASPECTS.

Variable	Successfully Processed	Not Successfully Processed	Absolute differences, 95% CI and p-value
Patient age (median, IQR)			
Patient sex (n, %)			
Minutes from stroke onset to scan (median, IQR)			
NIHSS (median, IQR)			
Stroke aetiology (n, %): • Ischaemia MCA territory • Ischaemia elsewhere • Haemorrhage • Mimic			
Presence of pre-stroke brain changes (n, %): • Atrophy • Leukoaraiosis • Old stroke lesions			
CT slice thickness (n, %): • ≤ 1 mm • > 1 mm ≤ 5 mm • > 5 mm			
Image quality (n, %): • Good quality • Movement artefacts • Streak artefacts • Patient malposition			

Note: IQR = Inter-quartile range. MCA = middle cerebral artery. NIHSS = National Institutes of Health Stroke Scale.

**Table 5. T5:** Variables for multivariable analysis and subgroups for diagnostic accuracy testing.

Clinical Characteristics		Imaging Findings		Imaging Technique	
Age	≤60 years	ASPECTS	<6	CT slice thickness	≤1 mm
	>60 years		≥6		> 1 mm
NIHSS	0–6	Infarct Location	MCA territory	Poor patient positioning	Yes No
	7–12		Elsewhere		
	>12	Atrophy, Leukoaraiosis, Old stroke lesion	Yes No		
Time from stroke onset to scan	<3 hours				
	3+ hours			Imaging artefact (movement or streak)	
Knowledge of affected side	Yes No				

**Table 6. T6:** Comparison of ICA-MCA axis occlusion identified by e-CTA and expert-human groups.

Human Readers e-CTA	Proximal Occlusion	Distal Occlusion	TOTAL
Proximal Occlusion			
Distal Occlusion			

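### Table 5 uses ASPECTS to predict, and to subgroup, an error that is built from ASPECTS, so part of the subgroup comparison is degenerate; separately, neither ordinal regression has a trial term

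*SAP article*

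**What the plan says.** Under Secondary outcomes, item 1, the SAP plans to find out which patient and imaging factors influence software accuracy: "we will perform multivariable ordinal logistic regression using the variables pre-specified in Table 5". The outcome is fixed in the next sentence: "The dependent variable will be the absolute difference in ASPECTS between e-ASPECTS and expert human readers", on a 0 to 10 scale. Table 5 is titled "Variables for multivariable analysis and subgroups for diagnostic accuracy testing". It lists ASPECTS <6 and ≥6 without saying whether the expert or the software score is meant. Continuous variables are dichotomised only for the subgroup step, so ASPECTS may enter the regression as the full score.

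For any variable significantly associated with poorer results, "we will also calculate and compare diagnostic accuracy figures (as above) for each of the subgroup arms". The general principles set the reference: "With expert human results as the reference standard, we will calculate true/false positive/negative cases". Primary outcome 1 gives the score cut-points: 10 v 0-9, 0-7 v 8-10, and 0-5 v 6-10.

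Trial is handled in one place: "For all diagnostic accuracy testing we will include random-effects meta-analysis modelling of individual patient data". Table 5 has no trial variable. Nor does the tertiary outcome model (2c and Table 10), whose covariates are age, NIHSS, time from onset, treatment and one software result. Section 2c itself notes: "Assessment of functional outcome after stroke varies among the RITeS trials", namely mRS at 90 days or OHS at 6 months.

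**The concern.** Two separate problems arise.

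First, a score is used to explain a difference of which it is one half. Rater error enters both sides of the regression, and a bounded scale leaves less room to disagree near 10. A significant ASPECTS effect could then be read as software failing in large infarcts when neither rater's accuracy has changed. The result would trigger a subgroup comparison whose arms coincide with the third cut-point, so some of its cells are empty by definition. The planned variance-inflation check does not help, because it compares predictors with each other and not with the outcome.

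Second, the plan pools studies whose readers were nominated by the trials and whose functional outcome differs in scale and timing, yet neither ordinal model separates trial differences from covariate effects. At stake are the stated reasons for software error and the claimed link between software output and clinical outcome.

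**Working it through.** The SAP gives no figure on this point to reproduce.

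**1. Subgroup cells.** Inputs: the Table 5 split; the three cut-points; the expert as reference; sensitivity = TP/(TP+FN); specificity = TN/(TN+FP). No assumption is needed.

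| Arm defined by | Arm | 0-9 v 10 | 0-7 v 8-10 | 0-5 v 6-10 |
|---|---|---|---|---|
| Expert | <6 | specificity 0/0 | specificity 0/0 | specificity 0/0 |
| Expert | ≥6 | both computable | both computable | sensitivity 0/0 |
| Software | <6 | sens. 100%, spec. 0% | sens. 100%, spec. 0% | sens. 100%, spec. 0% |
| Software | ≥6 | both computable | both computable | sens. 0%, spec. 100% |

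- Expert-defined <6 arm: every scan is reference-positive at each cut-point, so TN+FP = 0, PPV is forced to 100% and NPV to 0%. In the ≥6 arm at 0-5 v 6-10, TP+FN = 0.
- Comparing arms needs a figure from both. With expert arms, specificity can be compared at 0 of 3 cut-points and sensitivity at 2 of 3, so 2 of 6 comparisons exist.
- Software-defined arms: the <6 arm is all test-positive and its NPV is 0/0. One side of every comparison is therefore forced.

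**2. Does a difference appear when both raters are equally accurate?** Assumptions: independent errors, SD 1.2 for each rater, scores capped at 0 to 10.

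| True scores | Split by | Mean absolute difference, <6 | ≥6 | Gap |
|---|---|---|---|---|
| Skewed towards 10 | rated score | 1.37 | 0.96 | 0.41 |
| Skewed towards 10 | true score | 1.28 | 0.98 | 0.30 |
| Uniform | rated score | 1.19 | 1.17 | 0.02 |

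Splitting by true score removes the coupling but keeps the ceiling: 0.30/0.41 = 73% of the gap remains.

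A proportional-odds fit on the <6 indicator agrees (error SD 1.5; 40% of true scores at 10 and the rest skewed). The odds ratio is 2.08 with the expert score, 2.05 with the software score and 1.71 with the true score; ln 1.71/ln 2.08 = 0.54/0.73, or about 73%. On an unbounded scale the values are 1.24, 1.25 and 1.02, which isolates the coupling.

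**3. Trial.** Table 1, ischaemic studies: 104 + 98 + 3,035 + 65 + 113 + 271 + 1,149 + 293 = 5,128. IST-3 is 3,035/5,128 = 59%, and is the only one of the eight listed with 6-month follow-up. The entry for POSH shows no follow-up; without it the share is 3,035/5,015 = 61%.

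Illustration with these eight sizes: a covariate with no effect but with prevalence varying strongly by trial, and one cut of the ordinal outcome (200 runs per row). The between-trial SDs on the logit scale are assumed.

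| Between-trial SD | False positives at nominal 5%, no trial term | With trial fixed effect |
|---|---|---|
| 0.2 | 17% | 4% |
| 0.5 | 39% | 4% |
| 0.8 | 62% | 3% |

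**The case against.** The strongest reply is that the damage is limited. The subgroup step runs only if ASPECTS is significant. With expert arms, sensitivity in the <6 arm and specificity in the ≥6 arm are computable at all three cut-points. Accuracy for cause of symptoms, judged against follow-up, is not made empty by this split. A reader might infer that subgroup specificity is undefined throughout, or that the follow-up comparison cannot be computed at all. The SAP does not support that: Table 5 does not name the rater, and the 0/0 results need the expert score.

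Nor is the coupling the main source of a spurious effect. Most of it comes from the ceiling, which belongs to the outcome and can reach any correlate of lesion extent, such as NIHSS. With uniform scores it almost vanishes. Whether software errs more in large infarcts is also a fair question, and ASPECTS is the only direct measure of extent in Table 5.

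On trial, a reader might infer that every trial had its own separate readers and that the confidence intervals are certainly too narrow. The Patient population section says only that the trials nominated the readers, and describes very similar scoring methods, with five trials using the IST-3 approach; overlap is not excluded. No between-trial variance is given. The 59% counts patients in Table 1, not observations in either model, and measures no bias. The subgroup accuracy figures themselves do fall under the planned random-effects model.

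These limits stand. They leave the empty or forced cells and the two models without a trial term.

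**Conclusion.** The point holds in a bounded form. The degenerate cells follow from the SAP's own definitions and rest on no assumption, although they matter only if ASPECTS is significant. A spurious association of ASPECTS <6 with greater disagreement is possible under equal rater accuracy. Its size runs from nearly nothing to about 0.4 points at an assumed error SD of 1.2, depending on a score distribution that the SAP does not give.

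The missing trial term is plain from the text. Its consequence is conditional: covariates whose distribution differs by trial may be confounded with trial, and their intervals may be too narrow. The false-positive rates shown illustrate the mechanism under assumed between-trial SDs and do not estimate the bias in RITeS. One analysis is secondary and the other tertiary; no primary outcome is affected. The change is still worth making before unblinding.

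**What to change.** - Drop ASPECTS <6/≥6 as a subgroup for score-based accuracy.
- In the error regression, replace ASPECTS with a measure of extent independent of both baseline scores, for example from follow-up imaging, where available. Table 1 lists follow-up CT or MRI for all eight ischaemic studies, but follow-up extent is only a proxy for baseline extent. Otherwise omit ASPECTS and show error against the mean of the two scores on the Bland-Altman plot already planned. Either way, state that a ceiling effect remains.
- Add trial as a random intercept or a fixed effect to the Table 5 and Table 10 models. In the outcome model this also absorbs average differences between mRS at 90 days and OHS at 6 months.

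The cost is some SAP wording, one model term, slightly wider confidence intervals, and missing values where follow-up imaging is lacking.

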### Image processing

All CT scans will be processed by the RITeS team as follows:

1)In DICOM (Digital Imaging and Communications in Medicine) format2)On the cloud-based e-ASPECTS platform available at https://brainomix.com
3)Anonymised prior to web upload to remove patient identifiers, but retaining original trial identifiers, using modiCAS DICOM anonymizer (Erlangen, Germany).4)A person, trained in CT scan handling, will manually select the relevant scan for each patient using four criteria: I. First CT scan acquired after the patient reached hospital, if more than one available.II.Ideally native images (i.e. non-reformatted) acquired axially, but reformatted scans will be accepted if native imaging not available.III.The thinnest CT slices if more than one image set available.IV.Scans acquired using a soft-tissue kernel.At this stage, all scans meeting these criteria will be processed agnostic of patient or imaging characteristics. Scan selection for entry into the representative RITeS dataset will occur only once processing is complete, blind to imaging appearances and software results (see below).5)Scans will be batched into zip files of 10+ scans and uploaded to the Brainomix cloud-based platform.6)Affected side information will not be included at this processing stage but will be entered separately later for a proportion of cases.7)Any scan upload or processing failures will be recorded in a spreadsheet.8)Results will be exported from the Brainomix platform, using the standard export function and stored securely offline in .csv format.

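### Table 5 splits slice thickness only at 1 mm, so the subgroup accuracy figures cannot show whether a loss of accuracy lies above 5 mm, a band that Tables 3 and 4 keep separate

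*SAP article*

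**What the plan says.** Under Secondary outcomes, item 1 (processing success and factors influencing accuracy), the SAP article sets out two linked steps.

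- **Regression.** The dependent variable is the absolute ASPECTS difference between software and experts: "we will perform multivariable ordinal logistic regression using the variables pre-specified in Table 5".
- **Subgroup accuracy.** This step is conditional on the first: "For any variables found to be significantly associated with poorer e-ASPECTS results on regression testing", accuracy figures are calculated for each subgroup arm, and "for these analyses only, continuous data will be dichotomised as per Table 5".

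Table 5 is titled "Variables for multivariable analysis and subgroups for diagnostic accuracy testing". Its thickness entry has two arms: "CT slice thickness ≤1 mm" and, on the next row, >1 mm. The same table gives NIHSS three bands (0–6, 7–12, >12).

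The other two tables use three thickness bands. Table 4 lists "CT slice thickness (n, %): • ≤ 1 mm • > 1 mm ≤ 5 mm • > 5 mm". Table 3 has thin (≤1 mm) and thick (>5 mm) rows, with "Medium (> 1 mm ≤ 5 mm") between them.

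Image processing takes "The thinnest CT slices if more than one image set available", so a scan that exists only as thick slices stays in the study. The sampling rules also do not exclude imaging on quality.

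**The concern.** The plan treats 5 mm as a meaningful boundary when it describes the sample (Table 3) and when it compares processed with failed scans (Table 4). It drops that boundary, without giving a reason, at the one step that yields sensitivity and specificity by thickness. Every >5 mm scan is pooled with the 1–5 mm scans, and no accuracy figure for >5 mm scans is pre-specified.

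A stated secondary aim is to learn when and why e-ASPECTS is more or less accurate. If the regression flags thickness, the follow-up can report only ≤1 against >1 mm. It cannot say whether 1–5 mm scans perform acceptably while thicker ones do not. If a loss were confined to >5 mm scans, the >1 mm arm would show a value true of neither band.

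**Working it through.** The plan states no figure for this point, so there is none to reproduce. The check compares the tables and then works out how much a merged arm could dilute a loss.

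**1. The tables side by side**

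| Place | Use | Thickness bands |
|---|---|---|
| Table 3 | sample description | ≤1, >1 to 5, >5 mm |
| Table 4 | processed v failed scans | ≤1, >1 to 5, >5 mm |
| Table 5 | regression variables and accuracy subgroups | ≤1, >1 mm |

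Table 5 already holds a three-band variable (NIHSS), so a three-level subgroup is workable there. It also means that the word 'dichotomised' does not fit the table it refers to.

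**2. Inputs.** All are assumptions; the plan gives neither the thickness shares nor accuracy by thickness.
- 1000 lesion-positive scans.
- True sensitivity: 72% thin, 70% medium, 50% thick.
- Shares of all scans: 5–20% thin, 15–50% thick, the rest medium.

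**3. Formulas**
- Share of thick scans within the >1 mm arm: s = thick / (medium + thick).
- Sensitivity of the >1 mm arm = (1 − s) × 70% + s × 50%.
- Power, two-sided 5%, unpooled standard error: SE = √[p₁(1−p₁)/n₁ + p₂(1−p₂)/n₂], power ≈ Φ(|p₁−p₂|/SE − 1.96).

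**4. Results**

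| Thin / medium / thick (n) | s | >1 mm arm | ≤1 v >1 mm difference | Power |
|---|---|---|---|---|
| 50 / 800 / 150 | 15.8% | 66.8% | 5.2 points | 12% |
| 50 / 650 / 300 | 31.6% | 63.7% | 8.3 points | 25% |
| 50 / 450 / 500 | 52.6% | 59.5% | 12.5 points | 48% |
| 200 / 650 / 150 | 18.8% | 66.3% | 5.8 points | 36% |
| 200 / 300 / 500 | 62.5% | 57.5% | 14.5 points | 98% |

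First row in full: s = 150/950 = 0.158. The arm reads 0.842 × 70% + 0.158 × 50% = 66.8%. SE = √(0.72×0.28/50 + 0.668×0.332/950) = 0.065. Then 0.0516/0.065 − 1.96 ≈ −1.17, which gives power of about 12%.

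**5. With the bands kept apart.** Medium against thick is 70% v 50%, a 20-point difference, in every row. The lowest power in the assumed range is at 650 medium and 150 thick scans: SE = √(0.21/650 + 0.25/150) = 0.045, and 0.20/0.045 − 1.96 ≈ 2.5, so power is just over 99%.

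**6. Does the preceding regression still see the effect?** A small simulation used rank correlation as a stand-in for the ordinal regression. It assumed 2000 scans, 20% of them thin, and a mean absolute difference of 2.0 in >5 mm scans and 1.5 elsewhere. Continuous thickness detected the effect in 54% of runs when 10% of the >1 mm scans were thick, and in over 99% when 30% were. A split at 1 mm detected it in 8% and 49%. If thickness enters undichotomised, the regression therefore keeps much of the ability to flag an effect.

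**The case against.** A reader might infer that poor accuracy on thick slices would be averaged out of the plan altogether, so that it reports no thickness effect when a large one exists. The document does not support that. The dichotomy is stated to apply to the subgroup accuracy analyses only, which implies that thickness enters the ordinal regression undichotomised. That regression decides whether thickness matters, and the subgroup figures follow only if it says so. The power of the ≤1 v >1 mm contrast is therefore not the power of the plan to detect a thickness effect.

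Three further objections have force.
- Worse accuracy above 5 mm is assumed, not documented. If accuracy changes around 1 mm instead, the Table 5 cut is the informative one.
- Taking the thinnest available images can only lower the share of >5 mm scans, so a third arm may be small.
- The three tables do different jobs, and Table 5 is coarser than Table 4 elsewhere too: it merges movement with streak artefact. A coarser grouping is a choice, not in itself an error.

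These points limit the size of the concern but do not remove it. An odds ratio for absolute ASPECTS difference is not a sensitivity or specificity, and a single thickness term does not locate a loss above 5 mm. The planned covariate-adjusted ROC curves do not supply a figure for >5 mm scans either.

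**Conclusion.** The point holds in a limited form. The subgroup accuracy figures merge >5 mm with 1–5 mm scans, contrary to the bands in Tables 3 and 4, and so cannot show whether a loss lies above 5 mm. A loss confined to >5 mm scans can be diluted in them. In the assumed scenarios the >1 mm arm reads about 58–67% against true values of 70% and 50%. The visible difference from thin scans is 5–15 points with 12–98% power, where separate bands show 20 points with over 99%. Dilution is worst when thick scans are a minority and mild when they dominate; at the favourable end the existing split works well.

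All of these figures rest on assumed shares and sensitivities, and the conclusion about detection rests on thickness entering the regression undichotomised, which the text implies but does not state outright. The point is minor: it concerns a conditional step within a secondary outcome.

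**What to change.** - In Table 5, replace the two thickness arms with the three bands of Tables 3 and 4 (≤1, >1 to 5, >5 mm) for the subgroup accuracy figures. If the single 1 mm cut is kept, give the reason for it.
- In the Secondary outcomes text, change 'dichotomised' to 'categorised', which also fits the three NIHSS bands.

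The cost is one table row and one word, because Tables 3 and 4 already require the three-band data. The downside is one more subgroup arm, which may be imprecise if few scans exceed 5 mm; the confidence intervals already planned would show this. The change is best made before unblinding, since a >5 mm subgroup added later would be post hoc.
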